### **8.2.2 PROCEDURE IF A LOCAL REGROWTH IS DETECTED**

Patients with evidence of clinical or radiological local regrowth or pelvic relapse must be treated at least as urgently as a primary rectal cancer by the surgical team. Refer to suspected regrowth pathway in Section 8.2.3 below. Complete a **SURVEILLANCE CRF**. If patient proceeds to surgery Follow-up and CRF completion should be carried out according to the Control arm (Section 10.1, Assessment Schedule Control Arm and Section 11.1, Post-Surgery Follow Up). The **SURGERY, SURGICAL MORBIDITY** and **PATHOLOGY REPORTING Forms** should be completed when the patient undergoes surgery. If the colorectal MDT decision is to offer adjuvant therapy then the **CHEMOTHERAPY** and **TOXICITY Forms** should also be completed during treatment. The timing of the oncological outcomes, assessment of late surgical complications and PROMs should be completed as per protocol.

If patient refuses surgery or is not fit for surgery then a **DISCONTINUATION OF TRIAL TREATMENT Form** should be completed and the patient followed-up unless they withdraw consent to further data collection.

The patient is still eligible for analysis on an intention to treat basis.

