## 10. ASSESSMENT SCHEDULES

Please refer to the assessment schedules below for details of assessments to be performed, timelines and the CRFs to complete (further details relating to CRF completion can be found at the front of the CRF pack).

- Radiological assessment will be performed as per [Appendix 6](#) with synoptic reporting according to the allocated **POST-TREATMENT MRI FORM**.
- Chemotherapy toxicity will be assessed at the end of each cycle during treatment and residual toxicity assessed at the 12-month follow-up visit.
- When surgery is performed, surgical morbidity will be recorded intra-operatively and both early (6 weeks) and late (up to 12 months) surgical complications will be recorded post-operatively.
- **The QUALITY OF LIFE Form** will be completed by all patients at registration. For patients that undergo surgery the QoL forms should be completed again at 1 and 3 years following the completion of CRT. For patients who defer surgery the QoL forms should be completed at 1, 3 and 5 years from the time of CRT completion.
- Adverse events should be recorded from the date of the post-CRT MRI scan until 30 days after the patient's last dose of chemotherapy received during the intervention phase of the trial. Residual toxicity will be assessed at 12 months. Concurrent medications should be recorded at registration and updated from randomization until 30 days after the patient's last dose of chemotherapy. .
- **ANNUAL FOLLOW-UP Forms** should be completed at 12 months from the end of CRT and annually thereafter up to 3 years in those that undergo surgery and up to 5 years in those who defer surgery.

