## 10.1 ASSESSMENT SCHEDULE SUMMARY: CONTROL ARM

| CONTROL ARM                              |                        | REGISTRATION PERIOD    | INTERVENTION PHASE       |                    |     |                     |                      |                                                            | ANNUAL FOLLOW-UP       |    |    | DISEASE STATUS g |
|------------------------------------------|------------------------|------------------------|--------------------------|--------------------|-----|---------------------|----------------------|------------------------------------------------------------|------------------------|----|----|-----------------------------|
| VISIT TYPE                               | Prior to patient entry | Registration           | Randomisation (BASELINE) | Post CRT           | MDT | Surgery             | Surgical follow up   | Adjuvant Chemotherapy for 24 weeks                         | 12                     | 24 | 36 | 60                          |
| TIMELINES                                |                        | ≤ 4 weeks prior to CRT | During CRT h  | 4-6 weeks post CRT |     | 6-12 weeks post CRT | 6 weeks post surgery | Toxicity assessed at end of each cycle during chemotherapy | Months from end of CRT |    |    |                             |
| Informed consent a            |                        | X                      | X                        |                    |     |                     |                      |                                                            |                        |    |    |                             |
| Check eligibility criteria               |                        | X                      | X                        |                    |     |                     |                      |                                                            |                        |    |    |                             |
| Diagnosis, History & Clinical Assessment |                        | X                      |                          |                    |     |                     |                      |                                                            |                        |    |    |                             |

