| VISIT TYPE                        | Prior to patient entry | Registration           | Randomisation (BASELINE) | Post CRT       | MDT                                                                                                                                                                                              | No surgery | Chemotherapy for 24 weeks f                                         | Follow surveillance schedule for patient who defer surgery (Section 11.2.1) for a period of 5 years from end of chemotherapy. Complete SURVEILLANCE Form at each follow-up visit.

If surgery is undertaken (patient declines deferral of surgery or regrowth is detected during follow-up) then the follow-up schedule for the control arm should be used. The Surgery and Surgical Morbidity CRFs should be completed as per control schedule. In the case of regrowth a SURVEILLANCE CRF should also be completed. | 10 YEARS                       |
| TIMELINES                         |                        | ≤ 4 weeks prior to CRT | During CRT h  | 4-6 weeks post | Review of restaging MRI including mrTRG reporting. mrTRG directed management results in option of deferral of surgery (mrTRG I&II). The option of deferral of surgery is discussed with patient. |            | ≤12 weeks post CRT. Toxicity assessed at end of each cycle during chemotherapy |                                                                                                                                                                                                                                                                                                                                                                                                                                                                                                                                                  | From end of CRT                |

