## **11. CLINICAL FOLLOW-UP**

Once randomised, patients remain evaluable for the intent-to-treat analysis regardless of their subsequent course and treatment. Follow-up data on all patients, including details of other treatments given, is therefore important.

All patients that undergo surgery will be followed up for 5 years. Patients that defer surgery will be followed up for 10 years. In addition, where available, national mortality records and hospitals episodes statistics will be used to ensure long-term follow-up. If a patient fails to attend a clinic or cannot be followed up, the site should contact the patient's GP to assess their condition.

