Subjects with metastatic disease detected during follow-up will be treated according to the local MDT recommendation. If the MDT decides that palliative care is required, the patient will discontinue trial treatment and be classed as 'end of study' but still followed up (by completion of the **ANNUAL FOLLOW-UP Form**), with analysis for the primary endpoint assessed on an intention to treat basis.

**Patients with evidence of clinical or radiological local re-growth or pelvic relapse must be treated at least as urgently as a primary rectal cancer by the surgical team. Refer to deferral of surgery and regrowth pathways in Section 8.**

After surgery patients will receive the post-surgery follow-up as described in Section 11.1 above.

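### After surgery for regrowth the protocol leaves the follow-up horizon of a deferral patient unclear, its specific instructions make it outcome-dependent, and the late surgical morbidity form can fall due before the operation

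*Protocol*

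**What the plan says.** Three places deal with a patient who defers surgery and is later operated on for regrowth.

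- Section 10.2, follow-up column: "patient declines deferral of surgery or regrowth is detected during follow-up) then the follow-up schedule for the control arm should be used".
- Section 8.2.2: "If patient proceeds to surgery Follow-up and CRF completion should be carried out according to the Control arm (Section 10.1, Assessment Schedule Control Arm". It also points to the post-surgery rules of Section 11.1, and then adds: "The timing of the oncological outcomes, assessment of late surgical complications and PROMs should be completed as per protocol".
- Section 11.2: "After surgery patients will receive the post-surgery follow-up as described in Section 11.1 above".

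The timeline row of the control schedule in Section 10.1 is headed "Months from end of CRT". Its visits fall at 12, 24 and 36 months, with disease status at 60 months. A surgical morbidity entry stands at the 6-week post-operative visit and another in the 12-month column. Section 8.1 likewise dates the late morbidity form 12 months from completion of CRT.

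The general rules on duration are in Section 10, where annual forms run "annually thereafter up to 3 years in those that undergo surgery and up to 5 years in those who defer surgery", and in Section 11: "All patients that undergo surgery will be followed up for 5 years. Patients that defer surgery will be followed up for 10 years". In the Section 10.2 table the disease-status column reads 10 years from the end of CRT, and its footnote makes no exception for patients who are later operated on.

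**The concern.** A patient operated on for regrowth belongs to both of the groups that Section 11 names, and the two groups have different horizons. If the three specific instructions govern, length of observation inside the intervention arm is set by a post-randomisation outcome: patients whose deferral succeeds are observed for twice as long as those in whom it fails.

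The clock is a second problem. Control surgery follows CRT by weeks, so a late morbidity form 12 months after CRT works there. Surveillance of deferral patients runs for 5 years, so salvage surgery can come long after that form was due.

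Section 4 makes the safety of deferral something the trial must determine. Appendix 4 says that surgical morbidity matters most in patients operated on for regrowth after deferral. Section 4.4.2 lists late surgical morbidity, up to 12 months, as a secondary endpoint. The feasibility data are also to be pooled into the phase III analysis.

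**Working it through.** The plan states no figure on this point, so there is nothing to reproduce. The check is arithmetic on the plan's own schedule.

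**Inputs**
- Control surgery: 6–12 weeks after CRT (Section 8.1).
- Poor responders: chemotherapy starts within 12 weeks of CRT and lasts 12 weeks; surgery follows 6–12 weeks later (Section 8.3). A start no earlier than week 4 is assumed.
- Control schedule: annual forms at 12, 24 and 36 months, late morbidity form at 12 months, status at 60 months, all from the end of CRT (Sections 8.1, 10, 10.1).
- Sustained deferral: status at 120 months (Section 10.2).
- Month of salvage surgery: not given, so a range is shown, with surgery taken to fall in the month regrowth is detected.
- One week = 7/30.4375 = 0.23 months.

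**Formula:** months observed after surgery = horizon − month of surgery.

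**Other operated patients, to the 60-month status**
- Control: surgery at 6 × 0.23 = 1.4 to 12 × 0.23 = 2.8 months, leaving 58.6 to 57.2 months.
- Operated poor responders: earliest 4 + 12 + 6 = 22 weeks (5.1 months), latest 12 + 12 + 12 = 36 weeks (8.3 months), leaving 54.9 to 51.7 months.

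**Salvage after deferral**

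| Month of salvage | To 60-month status | Forms left at 12/24/36 | To late morbidity form | To 120-month status |
|---|---|---|---|---|
| 6 | 54 | 3 | 6 | 114 |
| 9 | 51 | 3 | 3 | 111 |
| 12 | 48 | 2 | 0 | 108 |
| 24 | 36 | 1 | already past | 96 |
| 36 | 24 | 0 | already past | 84 |
| 48 | 12 | 0 | already past | 72 |

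Counted from CRT, salvage patients reach 60 months like every other operated patient. Counted from surgery, theirs is the shortest observation once salvage falls later than about 8.3 months. At month 6 it overlaps the operated poor responders.

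**Late morbidity.** A control patient's late form comes 12 − 2.8 = 9.2 to 12 − 1.4 = 10.6 months after surgery. For salvage at month 9 it comes after 3 months, and from month 12 there is no interval left. Section 8.2.2 ties the surgical forms to the operation, which secures the early record, but leaves the timing of late complications as it stands. Section 8.2 itself asks for no surgical morbidity form at 12 months, so the only dated late forms are those in the operated pathways, all set from CRT.

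**Quality of life.** Section 10 gives operated patients forms at 1 and 3 years, and deferral patients forms at 1, 3 and 5 years. The switch drops the 5-year form.

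**Number of patients (illustration only).** 90 × 2/3 = 60 in the intervention arm; 60 × 0.30 = 18 deferrals; 18 × 0.20 to 18 × 0.40 = 3.6 to 7.2, about 4–7. The 30% is the Introduction's upper figure for complete or near-complete response, not an mrTRG 1–2 rate. The 20–40% regrowth is assumed. Poor responders who later convert to deferral are left out.

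**The case against.** A reader might go further and infer that failed deferrals have the shortest follow-up in the trial, that every salvaged patient loses years 5 to 10, and that long-term survival after deferral will look too favourable. The documents do not support that much.

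- **Clock.** On the trial's own clock, from CRT, 60 months is a tie with the other operated patients. Observation is shortest only when counted from surgery, and only for later salvage.
- **Unsettled text.** The switch in Section 10.2 sits in the follow-up column, while the disease-status column still reads 10 years. Section 11 gives 10 years to patients who defer, which these patients did. The closing sentence of Section 8.2.2 on timing could point back to Section 8.2, where annual forms run to 60 months. The control table also marks an annual follow-up entry at 60 months, against the 3 years in Section 10. Loss of years 5 to 10 is therefore one reading, although the more specific one.
- **Dated events.** The 60-month status records the date of recurrence or metastasis and the date of death. Fewer annual forms after salvage do not by themselves lose events up to 5 years.
- **Endpoints.** The feasibility endpoint is recruitment. The anticipated phase III endpoint, 3-year disease-free survival, is not shortened. Unsalvageable regrowth is captured through its own forms. No 5- to 10-year estimate is specified here.
- **Linkage.** Section 11 plans national mortality records and hospital episode statistics where available.

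All of this stands and limits the point. It does not remove the contradiction. Linkage is conditional and supplies neither protocol-defined recurrence nor Clavien-Dindo grades. The late morbidity defect does not depend on which disease-status horizon is chosen.

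**Conclusion.** The point holds in limited form. The protocol contradicts itself on how long a patient who deferred and was then operated on is followed. Its more specific instructions give 60 months from CRT, against 120 for sustained deferral, so follow-up in the intervention arm depends on outcome.

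Three items are at risk:
- late surgical morbidity after salvage, fully missed by the scheduled form when surgery comes at month 12 or later and cut short before that;
- the 5-year quality-of-life form;
- disease status from 5 to 10 years, only partly offset by record linkage.

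The conclusion rests on reading Sections 8.2.2 and 11.2 as overriding the general text of Section 11; the late morbidity item does not need that assumption. The number affected cannot be derived from the protocol, and 4–7 is illustrative. No bias in a planned analysis is shown. The reason to act is that these are the patients in whom the protocol itself says morbidity matters most, and data not collected cannot be recovered for the pooled analysis.

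**What to change.** Reconcile Sections 8.2.2, 10, 10.2, 10.3, 11 and 11.2 so that the data-collection horizon follows initial management:

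- Any patient who started deferral, including a poor responder who converted to it, keeps the ANNUAL FOLLOW-UP form and quality-of-life form to 5 years and records-based disease status at 10 years from the end of CRT, whether or not surgery follows.
- The early and late SURGICAL MORBIDITY forms are timed from the salvage operation, and Section 4.4.2 states that the 12 months for late morbidity count from surgery.
- The switch to the control data schedule is limited to patients who decline deferral at the outset.

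Clinical investigation and treatment after salvage stay as they are. The cost is an amendment to the wording, a few extra forms, and a 10-year status check that by the protocol's own footnote needs no clinic visit.

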### 10.3 INTERVENTION ARM -‘POOR RESPONSE’ TO CHEMORADIO THERAPY

| INTERVENTION ARM
POOR RESPONDERS |                              | REGISTRATION
PERIOD    | INTERVENTION PHASE          |                             |     |                                                                            |                                                                                                                                                                                                                                                                                                                                                                                                                                     |                                           |                            |                                                                     | ANNUAL
FOLLOW-UP    |    |    |    | DISEASE
STATUS i |
|-------------------------------------|------------------------------|---------------------------|-----------------------------|-----------------------------|-----|----------------------------------------------------------------------------|-------------------------------------------------------------------------------------------------------------------------------------------------------------------------------------------------------------------------------------------------------------------------------------------------------------------------------------------------------------------------------------------------------------------------------------|-------------------------------------------|----------------------------|---------------------------------------------------------------------|------------------------|----|----|----|--------------------------------|
| VISIT TYPE                          | Prior to
patient
entry | Registration              | Randomisation
(BASELINE) | Post
CRT                 | MDT | Chemo-
therapy
for 12 weeks                                          | MDT                                                                                                                                                                                                                                                                                                                                                                                                                                 | Surgery                                   | Surgical
follow
up   | Adjuvant
Chemotherapy
for 12 weeks                            | 12                     | 24 | 36 | 60 |                                |
| TIMELINES                           |                              | ≤ 4 weeks prior
to CRT | During CRT j     | 4-6
weeks
post
CRT |     | ≤ 12 weeks
post CRT.
Toxicity
assessed at
end of each
cycle | A further MRI scan should be performed 4-6 weeks from end of chemotherapy. If mrTRG now I or II the option of deferral of surgery should be discussed. If patients defers surgery patients should receive the remaining 12 weeks of chemotherapy and follow surveillance schedule in section 11.2.1 and assess disease status at 10 years (as for good response sub-group). If surgery performed follow-up according to this table. | 6-12
weeks
after
pre-op
chemo | 6 weeks
post
surgery | Toxicity assessed
at end of each
cycle during
chemotherapy | Months from end of CRT |    |    |    |                                |
| Informed consent a       |                              | X                         | X                           |                             |     |                                                                            |                                                                                                                                                                                                                                                                                                                                                                                                                                     |                                           |                            |                                                                     |                        |    |    |    |                                |
| Check eligibility criteria          |                              | X                         | X                           |                             |     |                                                                            |                                                                                                                                                                                                                                                                                                                                                                                                                                     |                                           |                            |                                                                     |                        |    |    |    |                                |
| Diagnosis & Clinical
Assessment  |                              | X                         |                             |                             |     |                                                                            |                                                                                                                                                                                                                                                                                                                                                                                                                                     |                                           |                            |                                                                     |                        |    |    |    |                                |
| Randomisation                       |                              |                           | X                           |                             |     |                                                                            |                                                                                                                                                                                                                                                                                                                                                                                                                                     |                                           |                            |                                                                     |                        |    |    |    |                                |
| Quality of life                     |                              | X                         |                             |                             |     |                                                                            |                                                                                                                                                                                                                                                                                                                                                                                                                                     |                                           |                            |                                                                     | X                      |    | X  |    |                                |
| Chemoradiotherapy                   |                              |                           | X                           |                             |     |                                                                            |                                                                                                                                                                                                                                                                                                                                                                                                                                     |                                           |                            |                                                                     |                        |    |    |    |                                |
| Blood sample b           |                              | X                         |                             | X                           |     | X                                                                          |                                                                                                                                                                                                                                                                                                                                                                                                                                     |                                           | X                          | X                                                                   | X                      | X  | X  |    |                                |
| Baseline MRI                        | X                            |                           |                             |                             |     |                                                                            |                                                                                                                                                                                                                                                                                                                                                                                                                                     |                                           |                            |                                                                     |                        |    |    |    |                                |
| Restaging MRI c          |                              |                           |                             | X                           |     | X h                                                             |                                                                                                                                                                                                                                                                                                                                                                                                                                     |                                           |                            |                                                                     |                        |    |    |    |                                |
| Surgery                             |                              |                           |                             |                             |     |                                                                            |                                                                                                                                                                                                                                                                                                                                                                                                                                     | X                                         |                            |                                                                     |                        |    |    |    |                                |
| Surgical Morbidity d     |                              |                           |                             |                             |     |                                                                            |                                                                                                                                                                                                                                                                                                                                                                                                                                     |                                           | X                          |                                                                     | X                      |    |    |    |                                |
| Pathology e              |                              |                           |                             |                             |     |                                                                            |                                                                                                                                                                                                                                                                                                                                                                                                                                     |                                           | X                          |                                                                     |                        |    |    |    |                                |
| Chemotherapy f           |                              |                           |                             |                             |     | X end of
each cycle                                                     |                                                                                                                                                                                                                                                                                                                                                                                                                                     |                                           |                            | X end of each
cycle                                              |                        |    |    |    |                                |
| Toxicity Assessment                 |                              |                           |                             |                             |     | X end of
each cycle                                                     |                                                                                                                                                                                                                                                                                                                                                                                                                                     |                                           |                            | X end of each
cycle                                              | X                      |    |    |    |                                |
| Annual follow-up                    |                              |                           |                             |                             |     |                                                                            |                                                                                                                                                                                                                                                                                                                                                                                                                                     |                                           |                            |                                                                     | X                      | X  | X  | X  |                                |

|                             |  |   |   |   |  |                     |  |   |   |                     |   |  |  |  |
|-----------------------------|--|---|---|---|--|---------------------|--|---|---|---------------------|---|--|--|--|
| Adverse events g |  |   |   | X |  | X end of each cycle |  |   |   | X end of each cycle |   |  |  |  |
| Concurrent medications      |  | X | X | X |  | X end of each cycle |  | X | X | X end of each cycle | X |  |  |  |

The **X** also denotes that CRFs need completing - tick or initial the boxes as the CRFs are completed.

a Eligible subjects will be asked to provide written informed consent at registration and at randomization.

b if patient has consented to additional blood sample collection for research.

c The post-CRT MRI should to be performed within 4-6 weeks (maximum of 10 weeks) from completion of CRT.

d Both early (4-6 weeks) and late surgical complications (up to 12 months) will be recorded.

e Resected specimen will be prepared and evaluated using a standardized method described in Appendix 5.

f Chemotherapy toxicity is assessed every 6 weeks during chemotherapy treatment. 12 weeks (6 cycles of FOLFOX or 4 cycles of CAPOX) are given pre-operatively and 12 weeks (6 cycles of FOLFOX or 4 cycles of CAPOX) are given post-operatively.

g All adverse events will be recorded from the date the Post-CRT MRI scan is performed until 30 days after the last dose of chemotherapy is administered during the Intervention Phase of the trial.

h A further MRI scan should be performed within 4-6 weeks from completion of pre-operative chemotherapy and mrTRG reported.

i Disease status at 5 years (does not require clinic visit): alive without metastatic or recurrent disease, alive with metastatic and/or recurrent disease (date diagnosed), dead (date of death)

j Patient consent to randomisation can take place at any time during CRT or once CRT is complete but at least 1 week prior to the post-CRT MRI scan

